**IV. STUDY DESIGN.**

- a. **Trial Design:** A multi-institution, randomized, single-blind clinical trial
  - b. **Participants and Exclusion Criteria:** Eligible subjects identified from the medical record will be those who are 1) scheduled to undergo RALP surgery, 2) willing to consent to the surgery being performed by one of the surgeons participating in the study, and 3) willing to be assigned by randomization to one of the two groups in the study. Exclusion criteria are 1) prior prostate surgery, ablation, radiation, or androgen deprivation therapy, 2) lack of 3 Tesla or 1.5 Tesla with endorectal coil preoperative MRI imaging, and 3) inability to give informed consent.
  - c. **Randomization:** Each case will be assigned to one of the two preparation methods by a randomization procedure that is stratified by surgeon. Each surgeon-specific randomization schedule will be prepared using permuted blocks of size 2; i.e., each 2-patient block will be some permutation of {VR-aided, Control}. Thus, each surgeon's cases will be randomized in a 1:1 ratio. Use of permuted blocks thus avoids any confounding of preparation method with temporal trends (e.g., trend due to a learning curve.)
- Sequentially numbered opaque sealed envelopes (SNOSEs) will be prepared for each individual surgeon. Each envelope will contain the treatment assignment for one case (intervention or control). There will be an equal number of envelopes containing intervention assignments and control assignments; the total number of envelopes provided to each surgeon will be determined based on the surgeon's historical/anticipated case volume. The treatment code will remain concealed inside the envelope until the moment the case is ready to be prepared.

- d. **Blinding:** Patients, personnel gathering data from the video review, and statistician will be blinded. Control and intervention groups identifiers will be known only to the research personnel opening the sealed envelope for random group assignment and extracting patient data from the electronic medical record.
- e. **Intervention:** For intervention cases, surgeons will be provided with a 3D model to view (a) prior to the operation in addition to the MRI and biopsy results and (b) during the operation in addition to the MRI. For control cases, surgeons will view only the MRI and biopsy results prior to the operation and during the operation itself.

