- f. **3D Model Creation and Delivery:** MRI scans will be deidentified and sent in Digital Imaging and Communications in Medicine (DICOM) format to Ceevra, Inc., where a patient-specific 3D model for each intervention patient will be created. The Prostate Imaging-Reporting and Data System (PIRADS) score will be used to identify and label prostate lesions. In addition, the biopsy report, will be used to create a patient-specific pathology map that will be included in the model to assist the surgeon in understanding the location of biopsy-proven cancer within the prostate. Models will be delivered to a mobile application on the surgeon's smartphone (Ceevra Reveal) and viewed as described above. In addition, the surgeon may view the model picture-in-picture on the robotic console screen using a video cable connection between the surgeon's smartphone and the surgical robot.
- g. **Outcomes Measures and Covariates:** The primary outcome measure is oncologic outcomes after RALP. This outcome will be measured at three time points: immediately postoperative, short term, and a final assessment when oncologic and functional outcomes have reached a steady state. Oncologic outcomes will be measured as margin status (positive or negative), PSA (linear and detectable/undetectable) at the initial assessment (which in most cases is three months postoperatively but may occur any time between 3 and 6 months), and PSA ( $>0.1$ ) at the final assessment (to be collected after 18 months but no later than 24 months). Additionally, any use of androgen deprivation therapy or radiation therapy will be captured at 24 months as an adverse oncologic outcome.
- Secondary outcomes are the urinary and sexual function of the patient, measured at the same three time points as above. For urinary function, this is bladder neck sparing (yes or no), measured immediately postoperatively, and incontinence pads per day, measured at both 3-6 months and 18-24 months postoperatively. For sexual function, this is nerve sparing (none, left, right, or bilateral), measured immediately postoperatively, followed by SHIM score, measured at both 3-6 months and 18-24 months postoperatively.
- Demographic data, disease-specific, surgery-specific, and surgeon-specific covariates will be collected from the medical record as well, see Appendix A.

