## Appendix A

### Study Covariates

#### 1. Patient parameters

- a. Age
- b. Race
- c. Surgeon ID and tier
- d. MRI Fusion Biopsy used
- e. Preop and postop Gleason score
- f. Preop PSA
- g. Preop SHIM score
- h. Preop use of erectile aid
- i. Prostate volume
- j. Number of masses
- k. Mass size
- l. Extracapsular extension
- m. Tumor location
- n. Tumor orientation
- o. PIRADS score
- p. Perineural invasion
- q. SV invasion
- r. Risk category
- s. Clinical stage
- t. Oncologic stage
- u. Number of positive biopsy cores
- v. Use of erectile aids (pre and postoperatively)

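### Preoperative pad use is not collected, so the pads-per-day outcome has no baseline to check balance on or adjust for

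*Combined protocol and SAP*

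**What the plan says.** Section IV.g of the combined protocol and SAP states: "Secondary outcomes are the urinary and sexual function of the patient, measured at the same three time points as above". Those time points begin immediately after the operation. The urinary measures are bladder neck sparing, recorded just after surgery, and "incontinence pads per day, measured at both 3-6 months and 18-24 months postoperatively". No urinary reading is taken before surgery.

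Entry under section IV.b is broad: "Eligible subjects identified from the medical record will be those who are 1) scheduled to undergo RALP surgery", with consent to a participating surgeon and to randomization. The exclusions are "prior prostate surgery, ablation, radiation, or androgen deprivation therapy", unsuitable MRI, and inability to consent. Continence and pad use are not mentioned.

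For covariates, section IV.g says: "Demographic data, disease-specific, surgery-specific, and surgeon-specific covariates will be collected from the medical record as well, see Appendix A". Among the patient parameters, Appendix A has "Preop SHIM score" and "Preop use of erectile aid". None of its three lists has a preoperative pad count, continence status or urinary score, and the surgeon surveys in Appendix B do not ask for one. Section IV.i compares baseline characteristics between the arms and, if they differ, moves to mixed models that use the listed covariates.

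**The concern.** A man who wears pads before RALP can enter the trial, and his postoperative pad count then includes use that the operation did not cause. For sexual function the plan provides the starting value that is needed to interpret the later score. For urinary function it does not.

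Section IV.i relies on a baseline comparison to decide whether adjustment is needed. For continence that comparison cannot be made from the planned data, so the plan's own safeguard does not reach this outcome. Three things are at stake. A chance imbalance in existing pad use would go unseen. A baseline covariate that could remove noise is not available to the model. The absolute pad counts reported in either arm would mix existing and new use.

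**Working it through.** **Is a baseline urinary value planned anywhere?**

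| Place | Sexual function | Urinary function |
|---|---|---|
| IV.b, entry criteria | no criterion | no criterion |
| IV.g, outcomes | nerve sparing; SHIM at 3-6 and 18-24 months | bladder neck sparing; pads per day at 3-6 and 18-24 months |
| Appendix A, patient parameters | preoperative SHIM; preoperative erectile aid use | none |
| Appendix A, technique and operative lists | none | none |
| Appendix B, surveys | planned and performed nerve sparing | planned and performed bladder neck preservation |

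The two outcomes are set up in parallel after surgery. Only one has a baseline value.

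**How large could a chance imbalance be?** The plan gives no figure to reproduce on this point, so what follows is an illustration.

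Inputs:
- 45 men per arm (section IV.h), allocated 1:1 within surgeon (section IV.c).
- Prevalence p of preoperative pad use. The documents do not give it; the assumed range is 1% to 10%.

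Let X and Y be the numbers of pad users in the two arms, taken as independent Binomial(45, p). Then

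P(|X − Y| ≥ 2) = 1 − P(X = Y) − P(|X − Y| = 1),

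and P(|X − Y| ≥ 3) is this value less P(|X − Y| = 2).

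At p = 0.05: P(X = Y) = 0.198 and P(|X − Y| = 1) = 0.347, so P(|X − Y| ≥ 2) = 1 − 0.198 − 0.347 = 0.455 (0.45499 before rounding, shown as 45%). With P(|X − Y| = 2) = 0.238, P(|X − Y| ≥ 3) = 0.455 − 0.238 = 0.217.

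| Assumed p | Expected pad users among 90 (90 × p) | Differ by ≥ 2 men | Differ by ≥ 3 men |
|---|---|---|---|
| 1% | 0.9 | 10% | 1.4% |
| 2% | 1.8 | 23% | 5.9% |
| 3% | 2.7 | 33% | 12% |
| 5% | 4.5 | 45% | 22% |
| 10% | 9.0 | 59% | 37% |

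These probabilities count imbalance in either direction. Imbalance that favours one named arm is half as likely.

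**How does that compare with ordinary sampling error?** Two men are 2/45 = 4.4 percentage points of one arm. For scale only, treat the outcome as any pad use, a yes/no reading that the plan does not define. With a proportion q in both arms, the standard error of the difference is √(2q(1 − q)/45):
- q = 20%: √(0.32/45) = 8.4 points, and 4.4/8.4 = 0.53
- q = 50%: √(0.50/45) = 10.5 points, and 4.4/10.5 = 0.42

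A gap of two men is thus about half a standard error.

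**The case against.** The strongest reply is that the trial compares randomized arms and does not estimate how much incontinence the operation causes. Existing pad use falls on both arms alike in expectation, and the between-group test already allows for chance imbalance. This stands. A reader might infer that existing incontinence is credited to the intervention, or that the urinary comparison is biased. The documents do not support either reading.

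A reader might also infer that existing pad use could never be separated afterwards. That goes too far. Section VIII has case data extracted from the site's EHR, and each site keeps a key file linking record number to study identifier. Preoperative pad use could be abstracted later wherever it was charted. The plan does not provide for this, however, and charting may be incomplete.

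Nor can one say that an imbalance of two or three men is as large as a plausible treatment difference. The plan states no expected difference in pad use, and two men are about half a standard error.

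Finally, the figures rest on an assumed prevalence. Near 1%, the effect is small. This also stands.

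The reply does not explain why the urinary outcome lacks the baseline that the sexual outcome has, or how section IV.i's baseline check could cover continence without one.

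**Conclusion.** The point holds as a modest, cheaply remedied gap in a secondary outcome. Pads per day is measured only after surgery, men who use pads are not excluded, and no preoperative urinary item is listed. The comparison between arms remains unbiased in expectation and the primary oncologic outcome is untouched. What is lost is the ability, within the planned dataset, to see or adjust for a chance imbalance, some precision, and a clear reading of the absolute pad counts.

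The chance of a gap of at least two men runs from 10% to 59% as the assumed prevalence runs from 1% to 10%. It takes pad use to be independent between men and every arm to reach 45. Since prevalence would not be recorded, a reader of the results could not tell which row of the table applies.

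**What to change.** 1. In Appendix A, section 1, add *Preop incontinence pads per day* beside the preoperative SHIM item, recorded before the randomization envelope is opened.
2. In section IV.i, include it in the baseline comparison and state that postoperative pads per day is compared between arms with adjustment for it.
3. As a supporting analysis only, repeat the comparison in men who used 0 pads before surgery.

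Cost: one more field to collect per patient. The protocol describes collection from the medical record and surgeon surveys and no study visit at which patients are questioned. Asking each man would therefore be a small added step at each site, and relying on the chart alone would leave some values missing. The supporting analysis loses the few men who used pads before surgery.

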- h. **Sample Size:** Sample size was calculated using prior data, including previous trials using 3D models in robotic partial nephrectomy. Previously we noted an effect size of 0.44 regarding the difference of outcome measures between 3D

model-aided and control groups. To account for multiple endpoints, we raised the sample size by 15%. Using the above method and paired t-test, the sample size of 90 (45 per arm) provided 80% power to detect clinically significant differences in our primary outcome measures with  $\alpha=0.05$ .

- i. **Statistical analysis:** Initial analysis will compare baseline characteristics between cases performed with (intervention) or without (control) models involved in preoperative planning. A two-sample t-test will be employed to compare means between groups and Chi-Square test or Fisher's exact test to assess the association between categorical variables. For outcome measures, the appropriate test will be used as described above to compare groups. To mitigate type I error due to multiple comparisons, and if the randomization yields balanced cohorts, a Bonferroni correction may be utilized for the primary and secondary outcomes. If randomization yields groups with statistically or clinically significant differences, adjusted differences between groups will be studied using a linear mixed model to regress the endpoint variables on covariates listed above, or the logistic mixed model, as appropriate.

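### Nerve sparing is compared between arms by body side, which hides any change in which nerve is spared relative to the tumour; changes in how many nerves are spared stay visible.

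*Combined protocol and SAP*

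**What the plan says.** Section IV.g places nerve sparing among the secondary outcomes, as the immediate measure of sexual function: "nerve sparing (none, left, right, or bilateral), measured immediately postoperatively". SHIM score follows at the two later time points.

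Section IV.i names a "Chi-Square test or Fisher's exact test to assess the association between categorical variables" and carries this over to the outcomes: "For outcome measures, the appropriate test will be used as described above to compare groups". An adjusted analysis is conditional ("If randomization yields groups with statistically or clinically significant differences") and takes the form of a "linear mixed model to regress the endpoint variables on covariates listed above, or the logistic mixed model, as appropriate".

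Section IV.f says that the pathology map in the 3D model is there to "assist the surgeon in understanding the location of biopsy-proven cancer within the prostate". Appendix A, under patient parameters, lists "Tumor location" as a covariate. No section combines the side spared with the side of the tumour.

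**The concern.** The model conveys where the cancer lies, so one plausible effect is on which nerve is spared relative to the cancer. The outcome is coded relative to the body. Suppose the model moves one-sided sparing from the tumour side to the opposite side, or the reverse. Men with left-sided tumours then move one way in the left/right table and men with right-sided tumours move the other way. With the sides about evenly split, the two movements cancel.

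The report could then show the same nerve-sparing distribution in both arms although the side choice had changed. The left/right split would also carry no information about tumour side, while costing the test a degree of freedom.

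**Working it through.** The plan gives no power or expected rates for nerve sparing; its 80% power statement concerns the primary outcome measures. There is therefore no figure to reproduce on this point.

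**Inputs from the documents.** 45 per arm and α = 0.05 (IV.h); four categories (IV.g); chi-square or Fisher's exact test (IV.i).

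**Assumptions, because the documents give no rates.** Sparing none/unilateral/bilateral is 20/40/40% in both arms. All tumours are unilateral, with a share q on the left. Among men spared on one side, the spared nerve is opposite the tumour in a stated percentage.

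**Cancellation.** Let t be the proportion spared on the tumour side only and o the proportion spared on the opposite side only.

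- P(left) = q·t + (1 − q)·o
- P(right) = q·o + (1 − q)·t

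At q = 0.5 both equal (t + o)/2, whatever the balance of t and o. Take 60% opposite-side sparing in control and 95% with the model:

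- Control: o = 0.40 × 0.60 = 0.24, t = 0.16, so left = right = 0.20.
- Model: o = 0.40 × 0.95 = 0.38, t = 0.02, so left = right = 0.20.

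The planned table is 20/20/20/40% (none/left/right/bilateral) in both arms. The test can only reject at its false-positive rate.

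**If sides are not evenly split.** In a slightly larger assumed swap (t from 0.20 to 0.02, o from 0.20 to 0.38, none 10%, bilateral 50%), simulated power under left/right coding is 5% at q = 0.5, 6% at 0.6 and 11% at 0.7. Tumour-side coding has 76 to 77% throughout. The cancellation is exact only at an even split, but little leaks through at moderate imbalance.

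**What tumour-side coding would gain.** Simulated Pearson chi-square, 45 per arm, 20/40/40 split, q = 0.5. The last column puts the 30% of men with bilateral or midline tumours in one category of their own.

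| Opposite-side sparing, control vs model | Expected men spared on tumour side only | Left/right coding | Tumour-side coding, all tumours unilateral | Tumour-side coding, 30% bilateral or midline |
|---|---|---|---|---|
| 60 vs 95% | 7.2 vs 0.9 | about 5% | about 54% | about 30% |
| 75 vs 95% | 4.5 vs 0.9 | about 5% | about 21% | about 11% |
| 85 vs 95% | 2.7 vs 0.9 | about 5% | about 8% | about 7% |

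The expected numbers are 45 × t; for example 45 × 0.16 = 7.2 and 45 × 0.02 = 0.9. Repeat simulations of the 60 vs 95% case gave 54 to 56%. Fisher's exact test was not simulated; the plan does not say when it replaces chi-square.

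**What stays visible.** Under the planned coding, with other assumed distributions, simulated power is 74% for bilateral sparing rising from 40% to 70%, 76% for bilateral sparing falling from 70% to 40%, and 89% for no sparing falling from 30% to 5%.

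**Dropping the left/right split.** Four categories in two arms use (4 − 1)(2 − 1) = 3 degrees of freedom; none/unilateral/bilateral uses 2. For bilateral sparing rising from 40% to 70%, with none and unilateral falling in proportion (20/40/40 to 10/20/70), power is about 68% with left/right coding and about 75% with three categories.

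**One catch-all category.** If the 30% of men with bilateral or midline tumours all go into a single outcome category, power for that same shift falls from about 68% to about 43%, because the number of nerves spared in those men is lost.

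**The case against.** The strongest reply is that nerve sparing stands under sexual function in IV.g, where what matters is none, one or both nerves. The planned coding still shows that. Side relative to the cancer bears on cancer control, which the plan measures separately through margin status and PSA. This stands, and it is why none/unilateral/bilateral should remain the sexual-function comparison.

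Second, control surgeons also see the MRI and biopsy results (IV.e), from which the model is built. They may already spare mostly opposite the tumour, and then recoding gains little: 8% power at 85 vs 95%. This stands too. A reader might infer that recoding turns an uninformative comparison into a well-powered one. The documents give no rates to support that, and power above 50% here needs a control rate near 60%.

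Third, Appendix B records planned nerve sparing by side before and after the model is viewed, and asks whether the plan was modified. A reader might infer that the trial is blind to changed decisions; it is not. But under V.a the preoperative survey covers intervention cases only, and the postoperative survey asks about nerve sparing performed only as yes or no. Neither gives a comparison between arms by side.

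The conditional adjusted model does not close the gap. It runs only if the arms differ, and tumour location as a main effect would not recover the swap; that needs an arm-by-side interaction or a recoded outcome.

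**Conclusion.** The point holds in a limited form. Comparing arms on left versus right carries almost no information about side relative to the tumour: with about evenly split unilateral tumours, a pure side swap is detected about 5% of the time. It does not follow that the plan would miss any effect on nerve sparing, since changes in the number of nerves spared remain detectable.

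The cancellation is algebra; the gain from recoding is not. Under the stated assumptions, power with tumour-side coding runs from about 54% down to 8% as control opposite-side sparing rises from 60% to 85%, and from about 30% to 7% if 30% of men have bilateral or midline tumours in a category of their own. This is a minor improvement to one secondary outcome and leaves the primary outcome untouched.

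**What to change.** In IV.g and IV.i:

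1. Keep left and right for data entry only.
2. Compare arms on none/unilateral/bilateral for the sexual-function outcome, in all men.
3. Prespecify a second derived comparison in men with a unilateral tumour by the recorded tumour location: none, opposite side only, tumour side only, bilateral.
4. Do not pool men with bilateral or midline tumours into one outcome category. They stay in the comparison under item 2 and are left out of item 3.
5. State whether the second comparison counts in the optional Bonferroni correction.

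The cost is small: one more secondary comparison, fewer men in the side comparison, and a check that the Appendix A tumour-location item records laterality, which the appendix does not define. No new patients, visits or procedures are needed. The change concerns coding and analysis only and makes no statement on which nerve should be spared.

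### The 80% power claimed for the primary outcome measures is not supported: most are yes/no with no event rate given, and 0.44 yields about 54% even for linear PSA at 45 independent patients per arm

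*Combined protocol and SAP*

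**What the plan says.** Sample size (IV.h): "Sample size was calculated using prior data, including previous trials using 3D models in robotic partial nephrectomy". The effect is introduced with "Previously we noted an effect size of 0.44 regarding the difference of outcome measures between 3D" model-aided and control groups; its type, endpoint and standard deviation are not given. A 15% increase is added for multiple endpoints. The conclusion is "Using the above method and paired t-test, the sample size of 90 (45 per arm) provided 80% power" for the primary outcome measures, at alpha 0.05 with sidedness unstated.

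Outcomes (IV.g): "Oncologic outcomes will be measured as margin status (positive or negative), PSA (linear and detectable/undetectable) at the initial assessment". To these it adds PSA above 0.1 at 18–24 months and any use of androgen deprivation or radiation therapy at 24 months. That is one continuous measure and four yes/no measures.

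Analysis (IV.i): means are compared by a two-sample t-test, and the plan names "Chi-Square test or Fisher's exact test to assess the association between categorical variables". Outcomes use the same tests as baseline characteristics.

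Design (IV.c): patients are allocated to separate arms, stratified by surgeon, and "each surgeon's cases will be randomized in a 1:1 ratio". Apart from blocks of two within surgeon, nothing pairs one patient with another.

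**The concern.** The power statement covers all the primary measures, but the calculation behind it fits at most one of them, and that one imperfectly. The power of a test on a yes/no outcome depends on the control event rate and on the difference sought. Neither appears anywhere in the document. An effect size of 0.44 for some other, unnamed measure does not supply them. The formula used is also paired, whereas the arms are independent and IV.i plans a two-sample test.

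What is at stake is how a negative result is read. Someone told that the trial had 80% power may take a non-significant result for margins, PSA above 0.1 or later treatment as evidence that the models do not help. In fact the trial may have had little chance of showing a benefit of plausible size.

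**Working it through.** **Inputs from the document.** 45 per arm, alpha 0.05, effect size 0.44, 15% increase, paired t-test (IV.h); outcome types (IV.g); tests (IV.i); independent 1:1 arms (IV.c).

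**Assumptions.** Two-sided tests, no dropout, control event rates of 10–50% (5% also tried), no multiplicity adjustment.

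**1. The plan's own figure.** The paired normal formula gives n = ((1.960 + 0.842)/0.44)² = 40.5 pairs. Times 1.15 this is 46.6, so 47 per arm and 94 in total. That is close to 45 and 90 but does not reproduce them. An effect of 0.45 would: (2.802/0.45)² = 38.8, times 1.15 = 44.6, so 45. The stated size is therefore nearly recovered, but only with a paired formula. For 45 pairs at 0.44 the exact paired-t power is 82%.

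**2. The continuous measure with independent arms.** The noncentrality is 0.44 × √(45/2) = 2.087. Normal power is Φ(2.087 − 1.960) = 55%; the exact two-sample t gives 54%. For 80% power, n = 2 × 40.54 = 81.1, so 82 per arm (83 by exact t), before the 15%. At 45 per arm, 80% power requires d of about 0.60.

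**3. The binary measures, with 0.44 translated in two ways.** Power was found by enumerating all 46 × 46 pairs of event counts at 45 per arm.

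- Cohen's h: 2·arcsin√p₁ − 2·arcsin√p₂ = 0.44. From 25%: 1.0472 − 0.44 = 0.6072, and sin²(0.3036) = 8.9%.
- Log odds ratio: 0.44 × π/√3 = 0.798, an odds ratio of 0.45. From 25%: odds 0.333 × 0.450 = 0.150, so 0.150/1.150 = 13.0%.

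| Reading of 0.44 | Chi-square (uncorrected) | Fisher's exact |
|---|---|---|
| Cohen's h, control rate 25% | 56% | 43% |
| Cohen's h, control rates 10–50% | 51–57% | 21–46% |
| Log odds ratio, control rate 25% | 32% | 21% |
| Log odds ratio, control rates 10–50% | 17–45% | 6–37% |

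**4. What 45 per arm can detect with 80% power.**

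| Control rate | Must fall to (chi-square) | Must fall to (Fisher) |
|---|---|---|
| 50% | about 22% | about 20% |
| 40% | about 15% | about 13% |
| 30% | about 8% | about 6% |
| 25% | about 5% | about 4% |
| 20% | about 3% | about 1% |
| 10% | not reached | not reached |

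At 10%, with no events at all in the intervention arm, power is 67% (chi-square) or 29% (Fisher). At 5% it is 19% or 2%.

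**5. How much is due to pairing.** For the continuous measure, moving from paired to independent arms takes power from 82% to 54%. On the h reading, chi-square at 45 per arm gives 51–57%, so yes/no data alone cost little more; Fisher's exact costs a further 10 to 30 points. At 83 per arm, for control rates of 10–40%, the h reading gives 77–81% (chi-square) or 64–76% (Fisher), and the odds-ratio reading 24–66% or 17–60%.

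The 15% increase is not tied to any adjusted alpha. If the Bonferroni correction that IV.i leaves optional were applied over five measures (alpha 0.01), power for the continuous measure at d = 0.44 would be 30%.

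**The case against.** The strongest reply is that the plan claims power for clinically significant differences without defining them, so no binary comparison has been shown to fall short. That stands in part. A reader might infer that the trial fails to deliver 80% power for the binary measures. The document supports only that 80% is not shown, because every binary figure above rests on an assumed control rate and a chosen translation of 0.44.

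Three other strong readings should be resisted.

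- That only near-elimination of events is detectable. This fits low control rates, but at 50% a fall to about 22% by chi-square is enough.
- That a two-sample formula would leave the problem untouched. On the h reading with chi-square, 83 per arm brings power to 77–81% for control rates of 10–40%. Much of the shortfall is therefore the paired formula. A corrected formula would still give no event rate or target difference for margin status, and Fisher's exact would still fall short.
- That 0.44 is a standardised mean difference from kidney surgery alone. The text says only effect size, and that the prior data include partial nephrectomy trials. Borrowing from another operation is a weak assumption, not in itself an error.

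The count also depends on whether androgen deprivation or radiation use, added in IV.g after the other measures, is primary. Either way most of the measures are binary.

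**Conclusion.** The point holds as an unsupported power statement. No translation of 0.44 tried here, at control rates of 5–50%, exceeds 57% power with 45 independent patients per arm. The continuous measure needs no assumed event rate: if 0.44 is its standardised difference, power is about 54%. The shortfall has three parts: the paired formula, which is the largest for linear PSA; the absence of any event rate or target difference for the binary measures; and the conservatism of Fisher's exact where it is used. Dropout before the 18–24 month assessment or a multiplicity adjustment would lower the power further. The correction should be made, but it concerns what the protocol claims and does not require a different sample size.

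**What to change.** Keep 90 patients and rewrite the end of IV.h:

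1. Delete the 80% power statement.
2. For margin status, state the detectable difference from the participating sites' pooled historical positive-margin rate, naming which IV.i test the figure uses. For example: *If the control rate is 25%, 80% power with 45 per arm (two-sided 0.05) requires a fall to about 4% by Fisher's exact or 5% by chi-square; if it is 40%, to about 13% or 15%.*
3. For linear PSA, state about 54% power at d = 0.44 by a two-sample t-test, and 80% only at d of about 0.60. Label 0.44 as an assumption from prior data that include another operation. Moving the 80% claim to this measure would not be correct.
4. State that PSA above 0.1 and androgen deprivation or radiation use will be read as estimates with confidence intervals if control rates are about 10% or lower.

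The cost is protocol wording and a short recalculation from existing site data, with no extra patients. The downside is that the stated power becomes less favourable.

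### The 15% increase does not account for the multiple endpoints: 80% power is stated only at unadjusted alpha 0.05, and falls to about 60% (5 tests) or 49% (11 tests) if the optional Bonferroni correction is applied

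*Combined protocol and SAP*

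**What the plan says.** Section IV.h builds the sample size in three steps.

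- Effect size: "Previously we noted an effect size of 0.44 regarding the difference of outcome measures between 3D" model-aided and control groups.
- Multiplicity: "To account for multiple endpoints, we raised the sample size by 15" per cent.
- Result: "Using the above method and paired t-test, the sample size of 90 (45 per arm) provided 80% power to detect clinically significant differences", at alpha 0.05. Sidedness is not stated.

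Section IV.i names one multiplicity method and makes it both optional and conditional: "if the randomization yields balanced cohorts, a Bonferroni correction may be utilized for the primary and secondary outcomes". It gives neither a number of tests nor an adjusted alpha.

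Section IV.g names oncologic outcome as primary and measures it in several ways: "Oncologic outcomes will be measured as margin status (positive or negative), PSA (linear and detectable/undetectable) at the initial assessment", then PSA above 0.1 "at the final assessment (to be collected after 18 months but no later than 24 months"), and finally "any use of androgen deprivation therapy or radiation therapy will be captured at 24 months as an adverse oncologic outcome". The secondary outcomes are bladder neck sparing, pads per day at two times, nerve sparing, and SHIM at two times. No single measure is designated as primary, and no testing order is given.

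**The concern.** IV.h tells the reader that multiplicity has been dealt with in the sample size, yet the power printed next to that statement is at the full 0.05. A larger sample leaves the false-positive rate of each test at its nominal alpha. Its only use here is to restore power after alpha has been reduced, and IV.h links the 15% to no reduced alpha.

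Two consequences follow, depending on how the option in IV.i is used. If the correction is applied, a null result would be read as coming from a trial with 80% power when the plan's own inputs give much less. If it is not applied, a nominally significant result on one of many measures would be read as protected when it is not.

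**Working it through.** **Inputs.** Effect d = 0.44, paired t-test, 45 pairs, alpha 0.05, 80% power and the 15% increase, all from IV.h. Two-sided testing is assumed.

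**Number of tests, counted from IV.g.** Primary, 5: margin status, PSA as a linear value, PSA detectable or not, PSA above 0.1 at final assessment, and androgen deprivation or radiation. Secondary, 6: bladder neck sparing, pads (two times), nerve sparing, SHIM (two times). Total 11. Other readings give 4 and 10 (adjuvant treatment not counted as primary) or 6 and 12 (its two components counted separately).

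**1. The plan's own figure.** The noncentrality is 0.44 × √45 = 2.95 on 44 degrees of freedom. Exact noncentral-t power at 0.05 is 82.3%, close to the printed 80%. The number of pairs for 80% is 42.5, so 43. One-sided testing would need 34 pairs (39 with the 15%) and gives 89.6% at 45, so it fits less well.

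**2. The 15% step.**

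- Exact t: 42.5 × 1.15 = 48.9, so 49; or 43 × 1.15 = 49.5, so 50.
- Normal approximation: ((1.960 + 0.842)/0.44)² = 40.5, and 40.5 × 1.15 = 46.6, so 47.
- In reverse: 45/1.15 = 39.1; with 39 pairs exact power at 0.05 is 76.4%.

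None of these gives exactly 45.

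**3. What 15% can buy.** To hold 80% power at alpha 0.05/m, the sample must grow by the factor ((z(1 − 0.05/2m) + 0.842)/(1.960 + 0.842))².

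| Tests m | z | Increase, normal approximation | Increase, exact paired t | Pairs needed |
|---|---|---|---|---|
| 2 | 2.241 | 21% | 22% | 52 |
| 5 | 2.576 | 49% | 50% | 64 |
| 11 | 2.838 | 72% | 74% | 74 |

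Solving for a factor of 1.15 gives alpha of about 0.031. Two Bonferroni tests already require 0.025.

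**4. Power with 45 per arm at d = 0.44 if Bonferroni is applied (exact t).**

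| Tests | Alpha | Paired t (IV.h) | Two-sample t (IV.i) |
|---|---|---|---|
| 1 | 0.05 | 82.3% | 54.2% |
| 4 | 0.0125 | 63.6% | 32.7% |
| 5 | 0.01 | 60.4% | 29.9% |
| 6 | 0.0083 | 57.8% | 27.7% |
| 10 | 0.005 | 50.5% | 22.2% |
| 11 | 0.0045 | 49.2% | 21.2% |
| 12 | 0.0042 | 48.0% | 20.4% |

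The two-sample noncentrality is 0.44 × √(45/2) = 2.09 on 88 degrees of freedom. By the normal approximation the paired figures are 64.7% for 5 tests and 54.5% for 11.

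**5. If Bonferroni is not applied.** For independent tests at 0.05, familywise error is 1 − 0.95⁵ = 22.6% and 1 − 0.95¹¹ = 43.1%. These do not depend on the sample size.

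**The case against.** The strongest reply is that the plan has no fixed Bonferroni level. The correction is permitted, not required; it depends on baseline balance; and no divisor is printed. This stands: 60% and 49% are conditional figures, not the plan's stated operating point. It does not rescue IV.h, because without the correction nothing in the plan controls familywise error across these measures, and the 15% cannot do so.

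The counts of 5 and 11 are also a reading of IV.g, which calls oncologic outcome one primary outcome with several measurements. The other readings shift power by only a few points. The family written in IV.i is primary and secondary outcomes together, so the 10-to-12 range is closer to its wording than the 4-to-6 range.

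A reader might infer that the printed sample size omits the 15% altogether. The documents do not show that. IV.h states no formula, and the normal approximation gives 46.6. If 0.44 is a rounded value that could be as high as 0.445, the same formula gives 39.6 × 1.15 = 45.6, within one patient of 45. What stands is that the step is not exactly reproducible as written.

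A reader might also infer that 30% or 21% is the trial's power for its primary outcome. That is not supported either. Four of the five measures counted as primary are binary and would go to chi-square or Fisher tests. A t-test at d = 0.44 describes only the linear PSA measure, and the documents give no event rates for the others.

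**Conclusion.** The statement that a 15% increase accounts for multiple endpoints is wrong as written, and the 80% applies only at unadjusted 0.05. On the plan's own paired calculation, power is about 82% at 0.05. If Bonferroni is applied, it falls to about 58–64% for 4 to 6 primary measures and about 48–51% for 10 to 12 primary plus secondary measures. At 5 and 11 tests that is roughly 20 and 31 points below the printed 80%. Keeping 80% would take about 50% more patients for five tests and about 73% more for eleven. If the correction is not applied, familywise error is about 23% or 43%.

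The assumptions are two-sided testing, d = 0.44, and, for the familywise figures, independent tests; these endpoints are likely to be correlated, so the familywise figures are indicative. The point stands even if the paired test is accepted. The mismatch between that test and the two-sample test in IV.i is a separate matter, and correcting it alone would leave the multiplicity claim unsupported.

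**What to change.** In IV.h:

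- Delete the statement that the 15% accounts for multiple endpoints.
- Show a derivation (formula, sidedness, rounding) that reproduces 45 per arm, or drop the 15% step.
- State which measures form the family, and restate power at the multiplicity-adjusted alpha that will be used.
- Compute that power for the planned test and label it as applying to a continuous measure at d = 0.44. On the two-sample t-test of IV.i it is about 54% at 0.05, 30% at 0.05/5 and 21% at 0.05/11.
- Give the binary primary measures their own power statement, with the assumed event rates written down.

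Holm's step-down procedure may replace Bonferroni in IV.i. It controls the same familywise error with no loss of power, and power at the fixed Bonferroni level is then a lower bound. This is optional and does not repair the 15% claim.

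The cost is protocol and SAP wording plus a short calculation. No patients are added; the downside is a less favourable stated power.
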